## Abstract

**Background:**

Suicide is a leading cause of death globally. Suicide deaths are elevated in those experiencing severe mental health problems, including schizophrenia. Psychological talking therapies are a potentially effective means of alleviating suicidal thoughts, plans, and attempts. However, talking therapies need to i) focus on suicidal experiences directly and explicitly, and ii) be based on testable psychological mechanisms. The Cognitive AppRoaches to coMbatting Suicidality (CARMS) project is a Randomised Controlled Trial (RCT) which aims to investigate both the efficacy and the underlying mechanisms of a psychological talking therapy for people who have been recently suicidal and have non-affective psychosis.

**Methods:**

The CARMS trial is a two-armed single-blind RCT comparing a psychological talking therapy (Cognitive Behavioural Suicide Prevention for psychosis [CBSPp]) plus Treatment As Usual (TAU) with TAU alone. There are primary and secondary suicidality outcome variables, plus mechanistic, clinical, and health economic outcomes measured over time. The primary outcome is a measure of suicidal ideation at 6 months after baseline. The target sample size is 250, with approximately 125 randomised to each arm of the trial, and an assumption of up to 25% attrition. Hence, the overall recruitment target is up to 333. An intention to treat analysis will be used with primary stratification based on National Health Service (NHS) recruitment site and antidepressant prescription medication. Recruitment will be from NHS mental health services in the North West of England, UK. Participants must be 18 or over; be under the care of mental health services; have mental health problems which meet ICD-10 non-affective psychosis criteria; and have experienced self-reported suicidal thoughts, plans, and/or attempts in the 3 months prior to recruitment. Nested qualitative work will investigate the pathways to suicidality, experiences of the therapy, and identify potential implementation challenges beyond a trial setting as perceived by numerous stake-holders.

**Discussion:**

This trial has important implications for countering suicidal experiences for people with psychosis. It will provide definitive evidence about the efficacy of the CBSPp therapy; the psychological mechanisms which lead to suicidal experiences; and provide an understanding of what is required to implement the intervention into services should it be efficacious.

**Trial registration:**

ClinicalTrials.gov (NCT03114917), 14th April 2017. ISRCTN (reference ISRCTN17776666 10.1186/ISRCTN17776666); 5th June 2017). Registration was recorded prior to participant recruitment commencing.

## Background

Suicidal thoughts, plans, and fatalities are of substantial concern worldwide. Approximately 800,000 lives are lost to suicide, globally, every year, which equates to one person dying by suicide every 40 s [1]. Estimates indicate that approximately 48,344 people died by suicide in the USA in 2018, which is 14.2 deaths per 100,000 population [2]. In the UK, for 2018 registrations, there were 6507 suicide fatalities, that is, 11.2 deaths per 100,000 population [3]. Suicide deaths increased in 2018 in the UK compared to 2013 figures [4]. In the US, the suicide death rate has also been increasing over time [5]. Suicide attempts are far more prevalent than suicide deaths, and suicide thoughts are more frequent than attempts. For example, as collected by the Adult Psychiatric Morbidity Survey, in 2014, 21.6% of British white people in England, UK, had suicidal thoughts whereas 6.9% had attempted suicide [6], and 0.01% had died by suicide that year. There were 1.4 million suicide attempts in 2017 in the USA [2] and 47,000 suicide deaths [7].

There is sound evidence that suicidal thoughts, plans, attempts and deaths are significantly elevated in those with severe mental health problems [8]. For example, mental health problems in those experiencing non-affective psychoses, or recent onset psychosis, have been associated with one of the highest, relatively unchanging, suicide mortality rates across the decades [9–12]. Whilst it is vital to focus on preventing deaths by suicide it is equally important to focus on reducing suicidal thoughts, plans and acts in people with severe mental health problems because they are both common and highly distressing for individuals and their families. For example, up to 50% of people with non-affective psychoses will experience suicidal thoughts and/or suicide attempts [10, 13]. Furthermore, suicidal thoughts and acts are associated with immense psychological distress [14] and can be strong predictors of suicide fatalities [15]. For instance, as reported by a recent meta-analysis, people with schizophrenia who also had thoughts of suicide were six times more likely to die by suicide compared to a 1.5 fold increase in those experiencing depression [16]. Hence, it is important that interventions which combat suicidal thoughts and acts are designed to attenuate a range of suicidal experiences, such as thoughts, urges, plans and attempts, in people with severe mental health problems such as psychosis.

A small number of meta-analytic systematic reviews have examined the extent to which psychological and psychosocial interventions reduce self-harm and suicidal experiences in those with mental health problems [17–21]. For example, two reported that psychological interventions were effective as long as they targeted suicidality (i.e., suicidal thoughts, behaviours and acts) or psychological precursors of suicidal experiences (e.g., hopelessness) rather than symptoms reflecting a psychiatric diagnosis [18, 19]. One of these reviews specifically evaluated the effects of cognitive-behavioural types of therapies (CBT) on suicide thoughts and behaviours [19]. Findings showed that cognitive behavioural therapies, including dialectical behavioural therapy, reduced suicidal thoughts and behaviours.

An issue with many studies included in such reviews is that few tested the effectiveness of a psychological talking therapy which, first of all explicitly focused on suicidal thoughts and acts, and second, were based on empirically supported recent psychological models which attempt to delineate the psychological pathways underpinning suicidal thoughts and behaviours. The Schematic Appraisal Model of Suicide (SAMS) [22] is one such recent psychological model of suicide which was developed from the influential Cry of Pain model [23] but also resonates with other contemporary psychological models of suicide, such as the Integrated Motivational Volitional Model [24–26]. These contemporary models converge, at least to some extent, in highlighting the importance of perceptions of emotional dysregulation, lack of social support and a perceived inability to solve inter-personal problems together with experiences of feeling defeated, trapped and hopelessness in pathways to suicidal thoughts and acts. It is important to understand mechanisms underlying suicidal experiences which are transdiagnostic and appear to be activated or triggered regardless of specific mental health problems or psychiatric diagnoses but to also recognise that specific symptoms associated with mental health problems, such as hallucinations, delusions, and hyperarousal may amplify suicidal thoughts, plans and acts [27–29].

Psychological therapies are optimally efficacious and effective if they focus on evidence-based, theoretically derived, psychological mechanisms thought to underlie suicidal thoughts and behaviours, and if as part of the therapy, they address such suicidal experiences explicitly [19]. Some of the cognitive behavioural therapies which have been evaluated may not always have been explicitly focused in this way. One psychological intervention approach which has focussed on ameliorating suicidal thoughts and acts is Cognitive Behavioural Suicide Prevention (CBSP) [14, 19, 30]. CBSP is based on the SAMS [22]. It was developed by the current authors and colleagues [14, 30, 31] as a psychological intervention designed to target suicidal thoughts, urges, plans and acts by focusing on perceptions of poor emotional regulation, social isolation, and difficulties with interpersonal problem solving. As these negative appraisals are posited to give rise to perceptions of being defeated, trapped and hopeless over time [32], and, in accord with a large body of evidence showing that these perceptions are central in the pathways to suicidal experiences [28, 32–42], CBSP also targets perceptions of defeat, entrapment and hopelessness. Hence, CBSP is unique in i. being grounded in a testable, evidence based psychological model of suicidal thoughts and acts, and ii. having an explicit and central focus on suicidal thoughts and behaviours.

Three pilot Randomised Controlled Trials (RCTs) have shown that the CBSP intervention is feasible and acceptable when adapted for use across a range of settings, and have suggested that it can be efficacious in reducing suicidal thoughts and acts. The first found reductions in measures of suicidal ideation and suicidal probability in people experiencing non-affective psychosis who lived in the community [30, 43]. The second, found that suicidal behaviours were less frequent in male prisoners following the CBSP intervention [31]. The third, found that this intervention was feasible, acceptable, and safe, and suggested that it may be cost-effective when used in psychiatric in-patient settings [44]. This means that the evidence from pilot RCTs across three diverse settings indicated that the CBSP suicide focussed therapy has the potential to counter suicidal experiences.

In order to develop this work further it is important to test the efficacy of CBSP in a larger, definitive, RCT in people with severe mental health problems who are vulnerable to suicidal experiences. It is also important to test the extent to which the underlying psychological mechanisms, on which CBSP is based are supported when applied to people with non-affective psychosis. Therefore, we propose to test CBSP adapted for people with non-affective psychosis (CBSPp) in an RCT, with two arms i. the CBSPp intervention plus treatment as usual (CBSPp plus TAU) and ii. treatment as usual (TAU) across three time points of baseline, 6 months follow-up (at therapy cessation), and 12 months follow-up. Our CARMS RCT is novel because i. it is founded on a testable psychological theory, ii. it is based on pilot work in diverse settings of a suicide focused cognitive therapy, and iii. unlike many of the studies included in recent meta-analytic reviews [17–21], it attempts to understand the mechanisms and the efficaciousness of a psychological ‘talking’ therapy in a population of individuals with severe mental health problems who are highly vulnerable to suicidal thoughts and acts. A more complex trial design is inappropriate given that the CARMS RCT advances pilot work.

The primary outcome is suicidal thoughts and acts at 6 months following entry to the trial. It is predicted that i. suicidal thoughts and acts will be less frequent and less severe in the intervention condition compared to the control condition, measured at therapy cessation (6 months) and after a 12 month follow up (FU) period compared to baseline; ii. negative appraisals of social support, emotional regulation, and interpersonal problem solving will lead to stronger perceptions of being defeated, trapped and hopeless, which will in turn lead to suicidal thoughts and behaviours over time; and iii. the treatment condition will result in less severe negative appraisals, and reduced perceptions of defeat, entrapment and hopelessness compared to the control condition. A more exploratory prediction is that symptoms of psychosis, particularly positive symptoms of hallucinations and delusions and their associated distress, will strengthen the relationships between negative appraisals, perceptions of defeat, entrapment and hopelessness and suicidal thoughts and behaviours. The acceptability and cost-effectiveness of the intervention will also be examined. Regarding the CBSPp therapy, we will attempt to gain information about the therapy process, the therapeutic alliance, engagement and adherence.

## Methods/Design

### Patient and public involvement (PPI)

A central, and fundamentally important component of the CARMS RCT is that people who are Experts-By-Experience (EBEs) have been involved in the design and set up of this project. Indeed, some of the co-investigators on the CARMS trial have personal experience of suicidality. We have established a CARMS specific PPI group with suicidal experiences and severe mental health problems who will be invited to have direct involvement in all the research stages, decision making processes, and suicidality training processes, of the CARMS project throughout its duration. It is becoming increasingly recognized that this type of PPI involvement is essential in any research projects investigating mental and physical health issues including those with economic implications [45–48].

### Study design: the RCT

The CARMS trial involves both an RCT and a nested qualitative component within the design. The trial was registered with ClinicalTrials.gov (reference NCT03114917) where it was first posted 14th April 2017. It was also registered with ISRCTN (reference ISRCTN17776666 10.1186/ISRCTN17776666) with registration being assigned 5th June 2017). Registration was accepted before recruitment commenced. The design of the trial follows Consolidated Standards of Reporting Trials (CONSORT; http://www.equator-network.org/reporting-guidelines/consort/) and SPIRIT guidelines (Standard Protocol Items: Recommendations for Intervention Trials; http://www.spirit-statement.org/), and the TIDieR checklist and guide; Template for Intervention Description and Replication (*BMJ* 2014; 348:g1687).

The design is a single-blind RCT with two parallel arms. Outcome variables assessing suicidal experiences will be collected at baseline, and at 6 and 12 months follow-up time points. Data pertaining to clinical and mediational variables will be collected at baseline, after therapy cessation (6 months), and at the 12 month follow-up time point. Health economics measures (assessed over the previous 6 months) will be collected at baseline and at the 12 month follow-up time-point to allow comparison over the pre-trial and post randomization period. It is anticipated that up to 24 individual therapy sessions, of up to an hour, will be offered over 6 months. Participants will be independently randomised to one of the two trial arms, with stratification based on whether the participant is or is not prescribed anti-depressant medication (as this could affect the primary outcome variable) and the NHS sites over which the trial is being tested (see Fig. 1).

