##### Health economics measures

Participant-level costs will be generated for each participant in both the CBSPp treatment and TAU control arms. Costs will comprise the costs of the intervention, of TAU, and downstream costs. Costs will be constructed from a combination of trial-based resource use (NHS contacts and the Client Service Use Receipt Inventory [CSRI] amended for our trial, to monitor service use) with published unit costs, allowing comparison of CBSPp with TAU in terms of costs to the NHS and PSS. Several methods are available to collect resource-use. The most popular have been resource-use questionnaires, resource-use diaries, and electronic record searches [70–72]. The Clients Service Receipt Inventory (CSRI) [73] is a commonly used method for the retrospective collection of resource-use information which has been implemented in the economic evaluation of a variety of physical and mental health care interventions [74–77]. The CSRI covers a range of economic factors including participant’s use of health and social care services, accommodation and living situation, income, employment and benefits (the CSRI is available from the Database of Instruments for Resource-use Measurement [DIRUM] website: http://www.dirum.org/assets/downloads/634462388066137028-CSRI.pdf). Similarly to other studies, we are using a modified version of the CSRI, based on the format and questions of the CSRI but ‘modified’ to reflect the care pathways of our study participants. Examples include the use of mental health care services (community teams, crisis teams, inpatient psychiatric admission),

The EQ–5D-3 L can reflect different levels of psychosis symptomatology, be responsive to intervention effects [78–80], and correlates with the PANSS and Brief Psychiatric Rating Scale - Expanded (BPRS-E) [81]. However, the EQ-5D-3 L showed significant ceiling effects compared with PANSS and BPRS-E. The EQ-5D-5 L [82] is less prone to ceiling effects in a range of health problems [83–86] and the increased sensitivity of EQ-5D-5 L may also favour Quality-Adjusted Life-Years (QALY) gains even if the changes in utility are smaller [87]. Hence we will use will use the EQ-5D-5 L. QALYs will be calculated by attaching available utility weights to the health states generated from the EQ-5D-5 L, using area under the curve methods with an assumption of a linear change between time points, controlling for baseline.

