#### Economic evaluation

Patient-level costs will be generated for each participant in the treatment (CBSPp intervention plus TAU) and TAU alone arms of the trial. Costs will comprise those of the treatment arm, those of TAU arm, and downstream costs. Costs will be constructed from a combination of trial-based resource use (NHS contacts and the Client Service Use Receipt Inventory [CSRI] amended for our proposed trial, to monitor service use) with published unit costs, allowing comparison of treatment with TAU in terms of costs to the NHS and PSS. The CSRI [98] is a commonly used method for the retrospective collection of resource-use information which has been implemented in the economic evaluation of a variety of physical and mental health care interventions [75, 76, 99, 100]. The CSRI covers a range of economic factors including a participant’s use of health and social care services, accommodation and living situation, income, employment and benefits (CSRI is available from the Database of Instruments for Resource-use Measurement (DIRUM) website: (http://www.dirum.org/assets/downloads/634462388066137028-CSRI.pdf). Similarly to other studies, we are using a modified version of the CSRI, based on the format and questions of the CSRI but ‘modified’ to reflect the care pathway of our study participants.

Participant-level costs will be generated for each participant in the Treatment and TAU arms from a combination of trial-based resource use with published unit costs. The unit costs of resource use will be taken from publicly available sources including current editions of NHS reference costs and the Unit Costs of Health & Social Care [101, 102]. Costs will be compared between the two groups using a bootstrapped regression model (as the data are likely to be skewed).

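### Health-economic measures at baseline and 12 months only, with a 6-month look-back, leave the therapy period outside the CSRI and give no 6-month utility reading

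*Protocol article*

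**What the plan says.** The section Study design: the RCT sets the schedule: "Health economics measures (assessed over the previous 6 months) will be collected at baseline and at the 12 month follow-up time-point". It gives the purpose in the same sentence: "to allow comparison over the pre-trial and post randomization period".

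The same paragraph treats the other main measures differently. For suicidality: "Outcome variables assessing suicidal experiences will be collected at baseline, and at 6 and 12 months follow-up time points". Clinical and mediational variables are likewise "collected at baseline, after therapy cessation (6 months), and at the 12 month follow-up time point". Therapy fills the first half of follow-up: "up to 24 individual therapy sessions, of up to an hour, will be offered over 6 months".

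On costs, the section Economic evaluation says: "Costs will comprise those of the treatment arm, those of TAU arm, and downstream costs". Both that section and Health economics measures build participant-level costs from two sources, NHS contacts and a modified CSRI. Neither gives the period that the NHS contacts cover. The CSRI is described as a retrospective instrument, modified to reflect the participants' care pathways, with community teams, crisis teams and psychiatric admissions as examples.

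On QALYs, the section Health economics measures attaches utility weights to EQ-5D-5L health states, "using area under the curve methods with an assumption of a linear change between time points, controlling for baseline". It gives the EQ-5D-5L no schedule of its own.

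**The concern.** The stated times, recall window and purpose do not fit together. A 6-month look-back taken at 12 months begins where therapy ends. The CSRI then records nothing of the usual care, crisis contacts or admissions in either arm while therapy is being given. Those are services that a suicide-focused therapy might plausibly change in that period. The therapy itself will be costed for those months, because therapists log attendance and session length.

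The utility problem is separate and does not come from the look-back. With readings at baseline and 12 months only, an area-under-the-curve QALY cannot register anything that happens at 6 months, when therapy stops and the primary outcome is measured.

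What is at stake is the cost-effectiveness question, which the Background lists among the trial's aims. An analysis plan written later cannot use readings that were never taken.

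**Working it through.** The plan gives no figure to reproduce here, so the check is interval arithmetic for the CSRI and trapezoidal area for the QALY.

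**CSRI coverage.** Inputs from Study design: the RCT: assessments at months 0 and 12, look-back 6 months, therapy in months 0 to 6.

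- Baseline window: 0 − 6 = −6, so months −6 to 0.
- 12-month window: 12 − 6 = 6, so months 6 to 12.
- Overlap with the post-randomisation year (0 to 12): 0 + 6 = 6 of 12 months, or 50%.
- Overlap with the therapy period (0 to 6): 0 + 0 = 0 of 6 months.
- With a further 6-month assessment and the same look-back (window 0 to 6): 6 + 6 = 12 of 12 months, and 6 of 6 therapy months.

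**QALY.** Let u0, u6 and u12 be utility at 0, 6 and 12 months, with time in years.

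- Two points, as scheduled: 0.5 × (u0 + u12).
- Three points: 0.25 × (u0 + u6) + 0.25 × (u6 + u12) = 0.25 × u0 + 0.5 × u6 + 0.25 × u12.
- Three-point minus two-point: 0.5 × [u6 − (u0 + u12)/2].

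The bracket is the departure of 6-month utility from the straight line. For departures of 0.02, 0.05 and 0.10, the error is 0.010, 0.025 and 0.050 QALY per participant. If both arms depart equally, the errors cancel in the comparison. Only the between-arm difference in departure matters.

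Now take d6 and d12 as the between-arm utility gains at 6 and 12 months, with no difference at baseline. The two-point gain is 0.5 × d12. The three-point gain is 0.5 × d6 + 0.25 × d12. The document gives no utility values, so these gains are assumptions chosen to span the possible shapes:

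| Assumed course | d6 | d12 | Two-point | Three-point | Two-point result is |
|---|---|---|---|---|---|
| Gain by 6 months, kept | 0.05 | 0.05 | 0.025 | 0.025 + 0.0125 = 0.0375 | too low by 0.0125 |
| Gain by 6 months, lost | 0.05 | 0 | 0 | 0.025 + 0 = 0.025 | too low by 0.025 |
| Steady accrual | 0.025 | 0.05 | 0.025 | 0.0125 + 0.0125 = 0.025 | correct |
| Gain only after therapy | 0 | 0.05 | 0.025 | 0 + 0.0125 = 0.0125 | too high by 0.0125 |

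Controlling for baseline does not repair this. It adjusts for u0, whereas the missing quantity is u6.

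**The case against.** Several points on the other side have force.

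- **A second cost source exists.** NHS contacts are named alongside the CSRI, and the text lists electronic record searches among available methods. Types of usual care are to be documented where possible, and case notes and adverse-event records are used where feasible for the suicidality outcomes. A reader might infer that no cost data will exist for months 0 to 6, or that the therapy is charged in full with nothing to set against it. The document does not support that, because it leaves the period of the NHS contacts open. This objection stands: the gap is in CSRI self-report, and service use may be recoverable.
- **Bias is not established.** A reader might infer that the two-point QALY must undervalue the therapy. The table shows otherwise: steady accrual gives no error, and a late gain is overstated. This stands too.
- **The stated purpose can be read modestly.** Two windows of 6 months each do allow a like-for-like comparison of service use before and after. But the later window starts only when therapy has ended, so it represents half of the post-randomisation period, and costing the intervention together with usual and downstream care needs the other half.
- **The schedule may be fuller elsewhere.** This is a condensed article, and Fig. 1 was not available in the text reviewed. It might list a 6-month economic assessment. If so, it contradicts the sentence in Study design: the RCT. As the text reads, the two-point schedule is explicit and not an omission through brevity.
- **Burden.** Fewer questionnaires is a legitimate choice in this population. The 6-month assessment takes place anyway, so the extra load is small.

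**Conclusion.** The concern holds in limited form. On the stated schedule, the CSRI covers 6 of 12 post-randomisation months and none of the therapy period, and no utility is read between 0 and 12 months. This does not fit the stated purpose of the schedule or the promised cost components.

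The two-point QALY difference is wrong by 0.5 times the between-arm departure at 6 months from the straight line. Under the assumed gains above, that runs from 0.025 too low to 0.0125 too high, with zero possible. The size and direction of any bias are unknown, and the text does not license calling the cost-effectiveness result biased. Nor does it license calling all the missing data irrecoverable: that is true of a 6-month utility reading that has passed, but service use may still be obtained from records.

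The conclusion assumes that the scheduling sentence applies to the EQ-5D-5L as well as the CSRI, which is the natural reading since no other schedule is given. It touches the economic evaluation only, and the primary efficacy analysis is unaffected. It should be fixed, but it does not threaten the trial's main result.

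**What to change.** - Add the modified CSRI (previous 6 months) and the EQ-5D-5L to the existing 6-month assessment, and compute QALYs from 0, 6 and 12 months.
- State the period and source of the NHS contact data, so that it is clear whether they cover months 0 to 12.
- For participants already past 6 months, take months 0 to 6 service use from NHS contact records, or extend the 12-month CSRI look-back to the date of randomisation. The second option asks for longer recall, and neither restores the 6-month utility.
- If Fig. 1 lists a 6-month economic assessment, reconcile it with the scheduling sentence in Study design: the RCT.

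The cost is a schedule amendment and two more questionnaires at an assessment that already takes place, with a small added burden on participants.
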